#### **3.6.2.2 Interim Analysis**

A pre-specified interim analysis is planned at 6 and 12 months after intervention initiation, evaluating the impact of the CDSS on secondary endpoints, including process-of-care measures and short-term clinical outcomes. The primary endpoint—

---

the composite rate of kidney- and cardiovascular-related hospitalizations—will be assessed after the full three-year follow-up period.

### **3.6.2.3 Health economics evaluation**

An economic evaluation of the CDSS intervention compared to usual care will be performed. Cost data for clinical events will be sourced via linkage with Beijing medical insurance database. Probabilities for disease progression to renal replacement therapy and cardiovascular events will be derived from the literature and analysis of insurance data. We will develop a Markov model using TreeAge Pro software to estimate incremental life years and quality-adjusted life years (QALYs) gained. Furthermore, sensitivity analyses will be conducted to explore the influence of age, different high-risk patient groups, and CKD stages on the results.

### **3.6.2.4 Qualitative Data Analysis**

Qualitative data will be collected through semi-structured interviews with primary care physicians and administrators from intervention centers. Interviews will explore user experience (e.g., usability, utility), implementation determinants (e.g., facilitators and barriers), and actionable strategies for system improvement. Thematic analysis will be performed on verbatim transcripts using NVivo software to identify key themes through an iterative, systematic coding process.

## **4. Research Quality Control**

As a pragmatic clinical trial, this study will focus its quality control efforts on two key areas: the implementation of the intervention and the management of study data. Following randomization, PCPs at all participating centers will receive standardized training on the trial procedures. Those in the intervention group will receive additional, comprehensive training on the use of the CDSS. In contrast, PCPs in the control group will not be introduced to the CDSS and will only receive training pertinent to routine patient management. This will ensure a consistent understanding of the processes among all sites. Throughout the trial, centers will be required to adhere strictly to the protocol specifications regarding randomization, allocation concealment, and participant eligibility. To maintain the quality of CDSS implementation in real-world settings, a three-tier management system will be established. This system will enable weekly feedback, evaluation, and verification of CDSS-related clinical quality indicators at each community site, allowing for timely identification and continuous improvement of any operational issues.

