This study is designed to address these gaps by developing a CKD-specific CDSS, contextualized for China's primary care setting through a multidisciplinary team that includes PCPs, nephrologists, and other specialists. A subsequent multicenter cluster-randomized trial will be conducted to evaluate the effectiveness of this CDSS versus usual care on both process measures and clinical outcomes. The CDSS will provide comprehensive support, encompassing screening, diagnosis, and management guidance. To isolate the effect of CDSS from that of general CKD training, government-supported CKD training will be provided to both study arms. This innovative approach aims to validate a scalable model for early CKD prevention and

---

control in Chinese communities, thereby ultimately generating evidence-based support to alleviate the CKD disease burden.

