### 3. Research Design

This study employs a multicenter, parallel-group, cluster-randomized controlled trial design. A total of 30 community health centers in the Xicheng District of Beijing will be recruited, with each center constituting a cluster. The study population consist of adult CKD patients and patients at high-risk for CKD-who are regularly managed at these centers, defined as having two or more visits documented in the Electronic Health Record (EHR) system during a designated 12-month screening period. Baseline characteristics, including CKD diagnosis (based on ICD codes) and clinical measures (e.g., the most recent blood pressure, HbA1c, and LDL-c values), were all ascertained from data recorded during this screening period. These 30 clusters will be stratified by their annual patient visit volume (large, medium, small) and subsequently randomized in a 1:1 ratio to either the intervention or control group. Following randomization and prior to the formal initiation of the intervention, both groups will receive the government-supported structured training. The intervention group will then implement a CKD-specific CDSS integrated into their existing EHR platforms, in addition to providing government-supported structured training. The control group will continue with usual care, also supplemented by the same government-supported training to isolate the effect of the CDSS itself. The trial will employ a two-phase evaluation scheme: a 6-month initial phase assessing the impact of the CDSS on process measures (CKD diagnosis, RAASi/SGLT-2i use) and short-term clinical control rates (blood pressure, HbA1c, LDL-c), and the final 36-month phase evaluating its effects on the primary composite endpoint of kidney and cardiovascular hospitalization rates, alongside a comprehensive health economic analysis, which will be conducted through linkage with the centralized Beijing Health Insurance Database.

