### **3.2 Study Interventions**

This study employs a multi-faceted intervention strategy, comprising a structured training program for PCPs and the implementation of a CDSS within the EHR infrastructure of community health services in Beijing Xicheng District, with administrative support from the Beijing Municipal Government and Xicheng District Health Commission.

---

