#### **3.4.2 Randomization and Intervention Allocation**

Stratified cluster randomization is employed at center level. Prior to the study, the 30 centers are stratified into three categories based on annual outpatient visit volume: large ( $\geq 10,000$  visits/year), medium (1,000–9,999 visits/year), and small ( $< 1,000$

---

visits/year). Within these strata, an independent statistician uses a computerized system to randomly assign centers in a 1:1 ratio to the intervention group (CDSS plus usual care) or the control group (usual care alone). Randomization results are concealed until the start of the intervention assignment.

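### Weekly indicator feedback that supports the CDSS is missing from the described intervention, so the trial tests CDSS plus feedback and does not isolate the CDSS itself

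*Protocol*

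**What the plan says.** Protocol 3.2 describes the intervention as "comprising a structured training program for PCPs and the implementation of a CDSS within the EHR infrastructure". Section 3.4.2 randomises centres to the "intervention group (CDSS plus usual care) or the control group (usual care alone". Neither place names any other component.

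Two passages explain why both arms are trained. The Background says: "To isolate the effect of CDSS from that of general CKD training, government-supported CKD training will be provided to both study arms". Section 3 goes further and describes the control arm as "also supplemented by the same government-supported training to isolate the effect of the CDSS itself".

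Section 4, on quality control, then adds an activity: "To maintain the quality of CDSS implementation in real-world settings, a three-tier management system will be established". Its content follows: "This system will enable weekly feedback, evaluation, and verification of CDSS-related clinical quality indicators at each community site". The sentence closes by saying that this helps to find and correct operational problems. For the other arm, the same section says that "PCPs in the control group will not be introduced to the CDSS and will only receive training pertinent to routine patient management".

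**The concern.** Regular return of clinical quality indicators to the places that deliver care can change practice whether or not decision support is present. If it happens in one arm only, it is a second difference between the arms, and equal training does not remove it. Here it is filed under quality control, so someone reading the intervention section would not know that it is part of what is tested.

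What is at stake is interpretation. A gain in coded diagnosis, renoprotective prescribing, screening or referral could come from the prompts, from the feedback or from both. The Background presents the trial as validating a model that can be scaled up. A district that installed the software without the management structure would not be reproducing what was tested.

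**Working it through.** No sample size, power or error-rate figure bears on this point, so there is nothing to recompute. The check sets the passages side by side.

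1. **Arms as declared (3, 3.2, 3.4.2).** Intervention: usual care + training + CDSS. Control: usual care + training. Difference: CDSS. On this list the Section 3 claim would be right.

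2. **Arms once Section 4 is added.** Intervention: usual care + training + CDSS + weekly indicator feedback. Control: usual care + training. Difference: CDSS + feedback. Training cancels; feedback does not.

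3. **Which arm receives it.** Section 4 does not say. The stated purpose is to sustain CDSS implementation, the indicators are tied to the CDSS, and control physicians are kept away from the system. All three point to intervention centres. If all 30 centres were meant, feedback would be balanced, but the control arm would no longer be usual care alone as 3.4.2 defines it. The text needs correcting on either reading.

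4. **What is fed back.** The indicators are described as clinical but are not listed. The nearest list is Table 5, which under Implementation gives the number of CKD referrals and the use of RAASi and SGLT2i. These correspond to secondary outcomes 4 and 2 in 3.3.2. Section 4 does not say that its indicators are these, but nothing in it excludes them.

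5. **How comparable support is handled.** Section 3.4.3 places on-site support in a run-in and leaves the run-in data out of the final analysis. The weekly feedback has no such time limit and no such exclusion.

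6. **Which outcomes are exposed.** Secondary outcomes 1 to 4 in 3.3.2 (diagnosis coding, RAASi/SGLT2i use, screening, referral) are direct actions of physicians, who are unblinded (3.4.5). They are the most open to misattribution. The hospitalisation endpoints lie further downstream, but they too would measure the package.

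7. **Costing.** Section 3.6.2.3 compares the CDSS intervention with usual care and gives a source for the cost of clinical events. It does not mention the cost of running a three-tier management structure.

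**The case against.** The strongest reply is that this is ordinary fidelity monitoring. Section 4 says that the structure exists to keep implementation sound and to resolve operational problems. Section 3.2 calls the strategy multi-faceted. Secondary outcome 9 calls the intervention complex and openly plans to optimise the CDSS and how it is implemented. The trial is pragmatic. The Background claims only to separate "To isolate the effect of CDSS from that of general CKD training", and shared training does that. On this view nobody promised to separate the software from the support needed to run it.

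Much of this stands. The Background sentence is correct as written, some of the system may be technical upkeep, and active management of implementation is signalled outside Section 4. Two things remain. What Section 4 returns each week is described as clinical quality indicators, which is more than system function. And the Section 3 sentence speaks of the CDSS itself, which goes beyond separation from training.

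A reader might infer more than the documents support:

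- **That feedback runs for all 36 months.** No start or end is stated. The phrase about the whole trial opens the preceding sentence, which concerns adherence to randomisation, concealment and eligibility. A count of feedback cycles would therefore be guesswork.
- **That physicians receive it.** Section 4 names no recipient.
- **That the trial result is biased or invalid.** Centres are still randomised, and the comparison estimates the effect of what was delivered. Only the label on that effect is wrong.
- **That the economic analysis will credit the oversight to the software.** Section 3.6.2.3 does not list which programme costs are counted, so the omission is possible but not stated.

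**Conclusion.** The point holds as one of attribution and description. The protocol states a property, isolation of the CDSS itself, that the design does not have on the natural reading of Section 4. The trial can validly estimate the effect of the CDSS with ongoing indicator feedback against trained usual care. It cannot say how much of that effect belongs to the CDSS alone, and the documents contain no figure that would allow the share to be estimated, so no magnitude is offered.

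The conclusion rests on two assumptions: that the feedback runs at intervention centres only, and that at least part of it concerns care rather than technical function. The wording favours both but states neither outright, and that silence is itself part of what needs correcting. The matter should be settled in the protocol because it changes what the trial can conclude, but it does not threaten the randomised comparison.

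**What to change.** - **3.2 and 3.4.2:** list the weekly feedback as a component of the intervention, delivered at intervention centres only. State which indicators are returned, to whom, how often, and from when until when. Cross-refer from Section 4.
- **Section 3, the objectives and the planned conclusions:** replace the claim to isolate the CDSS itself with the effect of CDSS with implementation feedback versus trained usual care. The Background sentence on separating the CDSS from training can stay.
- **3.6.2.3:** include the cost of the management structure in the intervention arm.

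There is no need to withhold clinical indicators from centres during the trial. That would redesign the planned implementation to cure a problem of description.

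The cost is protocol wording, a narrower claim and a slightly less favourable cost figure. Sample size, randomisation and data collection on outcomes are unchanged.

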## **5. Research Organization and Management**

The Principal Investigator (PI) will assume overall responsibility for the conduct of the study. The PI will establish an Academic Committee and a Trial Management Group (TMG) to collaborate with relevant stakeholders, including community health

---

managers, in overseeing all aspects of the trial. Responsibilities of the PI refer to preparation of the clinical trial application (including the study protocol and ethics submissions), site initiation and training, quality control, data management, statistical analysis, and study reporting. All trial-related documents will be accurately recorded and maintained in the trial master file.

## **6. Other Provisions**

### **6.1 Study Registration**

The trial will be registered with the Chinese Clinical Trial Registry Chi CTR (<http://www.chictr.org.cn>)

### **6.2 Publication Policy**

The primary trial results will be credited collectively to all co-investigators, study coordinators, and participating institutions. If named authorship is required, the writing committee chair will be listed first, followed by other contributors in alphabetical order. All trial investigators will be listed in the main publication. Findings from this study will be disseminated through presentations at international conferences and publications in peer-reviewed scientific journals.

### **6.3 Intellectual Property**

All results, data, and documents—in any form and whether derived directly or indirectly from this research—will be the property of the PI. The PI shall retain the right to use and develop these research outcomes without restriction, and will hold all relevant intellectual property rights.

|------------------------|------------------|--------------------------------------------------------------------------------------------------------------------------------------------------------------------------------------------------------------------------------------------------------------------------------------------------------------------------------------------------------------------------------------------------------------------------------------------------------------------------------------------------------------------------------------------------------------------------------------------------------------------------------------------|
| Type 2 Diabetes        | WHO              | E11                                                                                                                                                                                                                                                                                                                                                                                                                                                                                                                                                                                                                                        |
|                        | China            | E11.900                                                                                                                                                                                                                                                                                                                                                                                                                                                                                                                                                                                                                                    |
|                        | Beijing          | E11.901                                                                                                                                                                                                                                                                                                                                                                                                                                                                                                                                                                                                                                    |
| Hypertension           | WHO              | I10, I11, I12, I13, I15                                                                                                                                                                                                                                                                                                                                                                                                                                                                                                                                                                                                                    |
|                        | China            | I12.900x003, I13.900, I10.x00x002, I12.900, I10.x00, I11.900, I10.x09, I15.900, I11.901                                                                                                                                                                                                                                                                                                                                                                                                                                                                                                                                                    |
|                        | Beijing          | I13.901, I10xx11, I10xx02, I12.903, I15.901, I11.901                                                                                                                                                                                                                                                                                                                                                                                                                                                                                                                                                                                       |
| Cardiovascular Disease | WHO              | G45, I22, I48, I63/I64, I20, J81, I11.9, I50.0, I24, I61, I11.0, I48.0, I50, I25.103, I50.1, I23, I60, I48.1, I64, I13.0, I51.6, I48.2, I25, I21                                                                                                                                                                                                                                                                                                                                                                                                                                                                                           |
|                        | China            | I50.000, I21.900x017, I48.000, I50.904, I61.900, I50.100, I11.000, I48.100, I50.905, I50.000x006, I50.103, I50.900x018, I48.x00x015, I11.001, I48.200, I48.x01, I64.x00, I48.900x004, I50.104, I21.900, I50.105, I48.100x002, I20.900, I50.901, I50.900x007, I50.900x002, I11.002, I50.101, I48.x02, I50.902, I24.800, I13.000, J81.x00x002, I23.800, I50.102, I50.900x008, I48.x00x009, G45.900, I50.001, I50.907, I50.900x017, I25.103, I48.x00, I60.900, G45.900x001, J81.x00, I50.100x006, I50.002, I48.x00x023, I50.900, I25.900, I50.903, I48.x00x011, I50.900x009, I50.000x005, I11.900, I48.100x003, I50.908, I50.900x010, I51.600 |
|                        | Beijing          | I60.901, I25.105, J81xx01, I50.904, I50.905, I48xx15, I50.004, I50.103, J81xx02, I13.001, I48xx04, I11.001, I20.902, I50.106, I48xx02, I48xx08, I50.910, I50.006, I50.003, I21.902, G45.901, I50.902, I48xx13, I50.102, I48xx07, I48xx06, I50.107, I50.001, I50.907, I50.005, I50.909, I64xx02, I11.901, I64xx04, J81xx03, I50.917, I50.908, I48xx14, I48xx09, I50.911, I50.104, I48xx11                                                                                                                                                                                                                                                   |
| Acute Kidney Injury    | WHO              | N17, N01, T79.5, D59.3, K76.7, O90.4, O08.4, N99.0                                                                                                                                                                                                                                                                                                                                                                                                                                                                                                                                                                                         |
|                        | China            | N10.x00, N10.x01, N00.900x009, N10.x00x003, N12.x00x005, N17.001, N00.951, N00.901, N13.801, N17.251                                                                                                                                                                                                                                                                                                                                                                                                                                                                                                                                       |
|                        | Beijing          | N00.908, N10xx03, N10xx04+H20.9                                                                                                                                                                                                                                                                                                                                                                                                                                                                                                                                                                                                            |
| Obesity                | WHO              | E66.8, E66.2, E66.1, E66.9                                                                                                                                                                                                                                                                                                                                                                                                                                                                                                                                                                                                                 |
|                        | China            | E23.609, E23.605, E23.600x016, E66.100x001, E66.800, E66.100, E66.801, E66.901, E66.200x001, E66.900, E66.200                                                                                                                                                                                                                                                                                                                                                                                                                                                                                                                              |
|                        | Beijing          | E66.201, E23.609, E66.101, E66.801, E66.901, E23.616                                                                                                                                                                                                                                                                                                                                                                                                                                                                                                                                                                                       |
| Kidney stone           | WHO              | N20.2, N20.1, N20.0                                                                                                                                                                                                                                                                                                                                                                                                                                                                                                                                                                                                                        |
|                        | China            | N20.901, N20.001, N20.100, N20.002, N20.900, N20.200, N20.000                                                                                                                                                                                                                                                                                                                                                                                                                                                                                                                                                                              |
|                        | Beijing          | N20.003, N20.201, N20.901, N20.101, N20.000y003, N20.005, N20.902                                                                                                                                                                                                                                                                                                                                                                                                                                                                                                                                                                          |
| CKD                    | WHO              | N18.916, N18.917, N18.915, N18.914, N18.918                                                                                                                                                                                                                                                                                                                                                                                                                                                                                                                                                                                                |
|                        | China            | N18.803, N18.400, N18.200, N18.804, N18.500, N18.300, N18.801, N18.802, N18.001, N18.100                                                                                                                                                                                                                                                                                                                                                                                                                                                                                                                                                   |
|                        | Beijing          | N18.916, N18.917, N18.915, N18.914, N18.918                                                                                                                                                                                                                                                                                                                                                                                                                                                                                                                                                                                                |
| Pregnancy              | WHO              | O10.2, O26.8, O23.2, O22.1, O30.9, O15.2, O24, O12.0, O26.6, O15.1, O22, O33.0, O26.9, O15, O33.4, O22.3, O34.1, O12.2, O34.2, O14.2, O13, O23.0, O24.2, O23.5, O21.0, O12.1, O20.8, O26.0, O32.4, O22.0, O14.9, O34.8, O22.9, O34.3, O20.0, O30.0, O30.8, P08.0, O26.5, O22.2, O30.1, O33.5, O21.1, O25, O24.4, O22.4,                                                                                                                                                                                                                                                                                                                    |

|                           |         |                                                                                                                                                                                                                                                                                                                                                                                                                                                                                                                                                                                                                                                                                                                                                                                                                                                                                                                                                                                                                                                                                                                                                                                                                                                                                                                                                                                                                                                                                                                                                                                                                |
|---------------------------|---------|----------------------------------------------------------------------------------------------------------------------------------------------------------------------------------------------------------------------------------------------------------------------------------------------------------------------------------------------------------------------------------------------------------------------------------------------------------------------------------------------------------------------------------------------------------------------------------------------------------------------------------------------------------------------------------------------------------------------------------------------------------------------------------------------------------------------------------------------------------------------------------------------------------------------------------------------------------------------------------------------------------------------------------------------------------------------------------------------------------------------------------------------------------------------------------------------------------------------------------------------------------------------------------------------------------------------------------------------------------------------------------------------------------------------------------------------------------------------------------------------------------------------------------------------------------------------------------------------------------------|
|                           |         | O23.4, O23.3, O10.0, O21.8, O10.3, O34.7, O25, O30.2, O23, O26.4, O33.2, O34.5, O26.2, O26.1, O21.9, O23.5, O26.7, O15.0, O22.8, O16, O34.4, O34.6, O23.1, O33.3, O14.1, O14.0, O10.1, O11, O99.0, O10.4, O20, O26.3, O22.5, O10, O21.2, O34.0, O33.1                                                                                                                                                                                                                                                                                                                                                                                                                                                                                                                                                                                                                                                                                                                                                                                                                                                                                                                                                                                                                                                                                                                                                                                                                                                                                                                                                          |
|                           | China   | O21.000, O34.004, O21.900, O26.200, O23.400, O33.102, O21.100, O23.901, O34.801, O30.801, O24.100x011/O24.100x021, O26.607, O26.700, O20.900, O21.001, O22.800, O22.900, O30.000, O34.701, O33.500, O10.201, O34.802, O24.400, O33.400, O26.701, O24.301, O15.000, O34.003, O34.805, O30.100, O34.101, O23.001, O15.101, O22.101, O30.200, O21.200, O25.x00, O26.802, O33.200, O34.601, O13.x02, O34.600, O10.401, O22.103, O24.000, O34.804, O26.805, O26.800, O26.300, O34.603, O34.402, O22.901, O34.806, O32.400, O10.101, O34.005, O24.200x001, O14.000, O26.500, O26.900, O10.900, O10.301, O15.900, O33.100, O15.201, O22.000, O34.300, O34.602, O26.604, O33.001, O26.100, O12.100, O22.801, O26.501, O34.400, O22.500, O23.300, O26.605, O26.602, O10.200, O34.001, O34.401, O13.x01, O33.501, O21.800, O33.101, O23.500, O20.800, O30.800, O26.606, O16.x00, O26.400, O22.400, O24.900, O33.301, O23.900, O26.804, O34.200, O10.001, O33.300, O15.001, O24.100, O11.x00, O23.200, O23.000, O26.807, O10.300, O99.007, O10.400, O22.102, O34.406, O22.100, O22.300, O26.000, O34.002, O24.200, O24.300, O34.102, O34.803, O34.800, O34.500, O14.101, O34.201, O22.200, O23.505, O24.000x011/O24.000x021, O34.301, O34.502, O13.x00, O99.006, O33.201, O15.100, O26.601, O34.403, O20.000, O14.100, O23.502, O34.404, O11.x01, O26.603, O15.200, O26.801, O22.104, O14.900, O12.200, O23.504, O25.x01, O34.700, O22.902, O26.806, O23.100, O23.501, O10.000, O23.101, O26.803, O33.002, O30.900, O23.503, O10.100, O24.300x001, O26.600, O34.501, O34.604, O12.000, O34.405, O23.506, O14.102, O99.005 |
